### Statistical Analysis Plan

#### Overview

R (R Foundation for Statistical Computing) will be used for data cleaning and main analyses. Distributions of key outcome variables will be assessed and transformed if necessary. Unless otherwise specified, hypothesis tests will be conducted using a 2-sided α level of .05.

EMA responses will be aggregated to derive scores for each of the 4 food parenting practice domains during each data collection period. Given the unequal number of questions related to each domain, 2 versions of domain scores will be created by computing (1) the number of items endorsed in each domain and (2) the proportion of items endorsed in each domain. Domain scores will be calculated for responses given at each event prompt (typically 2-8 per day over each 8-day data collection period).

Food parenting practice domain scores will be aggregated and compared visually and statistically at the event level (eg, breakfast, lunch, snack, and dinner) and by time period (eg, 9 AM to noon, 3 PM-5 PM, and 5 PM-9 PM). In addition, for each data collection period, we will fit linear mixed models for each domain of the form (M1) *D_ij_ = β_0_ + β_1_Z_ij_ + β_2_X_i_ + b_i_ + ε_ij_*, where *D_ij_* is the domain score for person *i* at event prompt *j*, *Z_ij_* is the event characteristic of interest (meal or time period indicator), *X_i_* is a set of baseline characteristics for person *i*, *b_i_* is a person-specific random effect, and *ε_ij_* is the residual. Longitudinal response patterns in domain scores will be visualized and qualitatively compared. We will calculate each individual’s SD, IQR, and entropy of domain scores across their longitudinal observations. How between-day fluctuations in food parenting differ across individuals will be quantified using longitudinal mixed models, similar to those described above, with the event characteristics *Z_ij_* representing between-day factors such as day of the week. The SD, IQR, and entropy of residuals from these models will also be summarized to characterize between-day fluctuations.

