The distribution of the summary measures (SD, IQR, and entropy) of the longitudinal models described above will be used to derive measures of the consistency and endurance of food parenting practices. A metric of within-day consistency across event characteristics (eg, meal type) will be derived by calculating the distribution of SDs of individual residuals from model (M1) and then calculating an individual’s *z* score relative to this distribution. For example, an individual whose food parenting practices fluctuate substantially across meals will have a large SD of residuals relative to the population, so their *z* score will be relatively large. Consistency *z* scores will be used as predictors of child dietary intake in aim 2. Endurance will be measured by applying a similar *z* score approach but with models that incorporate data across multiple data collection periods. For example, model (M1) will be expanded to include data from times T2 to T4, and endurance *z* scores will be calculated from the distribution of spread summary measures (SD, IQR, and entropy) of the residuals from this expanded model.

Individual food parenting practice domain scores, as well as consistency and endurance metrics, will be used as inputs to a k-means algorithm (implemented using the *kmeans* package in R) to identify clusters of parents observed to use similar food parenting practices over the data collection period. For example, this technique might distinguish subsets of individuals who consistently and primarily use structure and autonomy support practices and those who use these practices less consistently or more commonly use coercive and indulgent practices. We will apply the k-means algorithm with a modest number of clusters (3-5) to ensure that the resulting groups are of sufficient size to accurately characterize them. Descriptive statistics will be used to summarize and compare the food parenting practices as well as demographic and family characteristics of each cluster. Cluster stability metrics and qualitative assessment of the scientific meaningfulness of the clusters will be used to choose a final number of clusters that will define subgroups for inclusion in the following analyses.

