To examine the longitudinal impact of within- and between-day fluctuations in food parenting practices on child dietary intake, we will fit regression models for the outcome of child HEI measured from 24-hour dietary recall at time points T2 to T4. The main predictors of interest will be the individual-level summary measures of the 4 food parenting practice domains derived above. Our primary models will include the subgroup indicators classifying parents according to food parenting practice patterns, but we will also consider models that use average domain scores as well as consistency and endurance metrics. We will fit separate linear regressions for each data collection period, as well as longitudinal models that incorporate data across the time points T2 to T4. For period-specific models, we will include cluster indicators as well as consistency *z* scores that reflect the degree of within- and between-day fluctuations in food parenting practices during that period, along with relevant adjustment covariates. For longitudinal models, we will also include endurance *z* scores that reflect whether food parenting practices are maintained across data collection periods.

To identify momentary predictors of within- and- between-day fluctuations in the use of food parenting practices across time and context, we will combine the signal and event EMA survey data to understand how momentary factors (eg, mood, stress, and time constraints) affect food parenting practices. The main statistical approach will be to fit longitudinal linear mixed models of the form: (M2) *D_ij_* = *β_0_* + *β_1_W_ij_* + *β_2_X_i_* + *b_i_* + *ε_ij_*. Here, *W_ij_* represents a *vector* of momentary predictors, which will be derived by summarizing signal surveys within fixed time windows before the event *j*. Initially, we will define 

, with the superscript in parentheses indicating the number of hours before the event covered by that variable. For instance, 

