## Results

### Overview

Recruitment and data collection began in October 2023. At the time of this protocol paper’s submission, data collection is still in progress and is expected to continue through November 2026. A racially and ethnically diverse cohort was successfully enrolled, with 28.3% (72/254) of enrolled participants identifying as White and 71.7% (182/254) identifying as Black, Indigenous, or people of color. Refer to Table 2 for detailed information on the characteristics of the Preschool Plates baseline sample.

Hypotheses

This study hypothesized the following:

Use of food parenting practices will vary within- and between-days; unique patterns will emerge across time (eg, time of day and day of week) and context (eg, location and type of eating occasion).Distinct patterns in food parenting approaches will emerge; distinct pattern features will include mean levels of engagement in specific food parenting practices (by domain), as well as consistency in approach across day-, week-, and 6-month intervals, and endurance (or lack thereof) of patterns across time.Healthful eating occasion–level dietary quality (ie, Healthfulness of Meal Index assessed via EMA) will be positively associated with supportive feeding practices (eg, structure and autonomy support) and inversely associated with unsupportive practices (eg, coercive control and indulgent).Consistent and enduring use of supportive feeding practices will be associated with a more healthful overall diet quality (ie, HEI assessed via 24-hour dietary recalls) cross-sectionally and at 2-year follow-up, as compared to inconsistent or short-lived use of supportive practices and consistent and enduring use of unsupportive practices.We expect to identify numerous momentary predictors of significance (eg, mood, stress, child behavior, and time constraints). Parents will shift within the day from supportive feeding practices toward unsupportive feeding practices in response to momentary predictors (eg, high stress, low mood, or limited time).

**Table 2 table2:** Characteristics of the Preschool Plates baseline sample (N=254).

Characteristics		Values
Child age (y), mean (SD)		3.48 (0.59)

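### The endurance score pools event-level residuals over waves, so it mixes within-wave fluctuation with change between waves, ignores direction, and can rank a declining parent as more enduring than a stable one.

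*Protocol article*

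**What the plan says.** All references are to the protocol article. Statistical Analysis Plan, Overview, sets out M1 as a linear mixed model for a domain score at each event prompt. It has an event characteristic, baseline characteristics, a term b_i that "is a person-specific random effect, and" an event-level residual.

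Consistency is the z score of a parent's SD of M1 residuals within one data collection period; a parent who fluctuates more gets a larger value. Endurance applies a similar approach "but with models that incorporate data across multiple data collection periods". The worked case is that "model (M1) will be expanded to include data from times T2 to T4", after which endurance z "scores will be calculated from the distribution of spread summary measures (SD, IQR, and entropy) of the residuals from this expanded model".

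The same section later gives the intended meaning: the longitudinal models of the Healthy Eating Index (HEI) include endurance z "scores that reflect whether food parenting practices are maintained across data collection periods". Hypothesis 4 (Results) depends on that meaning: "Consistent and enduring use of supportive feeding practices will be associated with a more healthful overall diet quality", contrasted with inconsistent or short-lived use. Hypothesis 2 also treats consistency and endurance as separate features of a pattern. Both metrics are inputs to the k-means clustering, and the Power Analysis uses a median split on either one as its example.

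**The concern.** A single b_i, constant over waves, removes only the parent's all-wave mean. What remains in the residuals is ordinary variation between eating occasions plus any shift of that parent's wave means. Taking the SD, IQR or entropy of the pooled residuals merges the two sources, and none of the three records whether practice rose or fell. No person-by-wave effect, slope or wave-mean contrast is described that would separate them. A wave indicator in the fixed part would remove only the average change of the cohort, not an individual's.

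At stake is the reading of the endurance coefficient. If the score mostly repeats consistency, the longitudinal HEI models cannot say much about maintenance, and a null or positive coefficient could be reported as evidence on two-year persistence that it does not supply. The clusters would also count within-wave fluctuation twice.

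**Working it through.** **The plan's own figure.** The endurance metric has no stated figure. The nearest is the Power Analysis example of a median split on consistency or endurance: 80% power at 0.4 SD with 100 per group. A two-sample calculation at two-sided 0.05 gives 80.7%, and for 50 per group at 0.57 SD it gives 81.3%. Both reproduce, but neither bears on what the score measures.

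**Step 1: what the score contains.** For one parent,

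pooled residual variance ≈ within-wave event variance + variance of the wave means.

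**Step 2: ranking.** The item counts (structure 14, autonomy support 8, coercive control 6, indulgence 8) come from the Ecological Momentary Assessment section. The parents below are illustrations.

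- Structure domain, wave means 8, 8, 8, 8, event SD 2.5: √(0 + 6.25) = 2.50.
- Structure domain, wave means 9, 8, 7, 6, event SD 1.5: the variance of the means is 1.25, so √(1.25 + 2.25) = 1.87.
- On an 8-item scale, means 4, 4, 4, 4 with event SD 2 give √(0 + 4) = 2.00; means 5, 4, 3, 2 with event SD 1 give √(1.25 + 1) = 1.50.

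In both pairs the parent losing the practice scores as more enduring. Reversing the order to 6, 7, 8, 9 again gives 1.87, so direction is lost.

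**Step 3: sensitivity to drift.** Take event SD 1 and four waves. A drift of d in equal steps adds 5d²/36, and a step of d halfway adds d²/4.

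| d (event SDs) | Equal steps: pooled SD | Halfway step: pooled SD |
|---|---|---|
| 0.5 | 1.017 | 1.031 |
| 1 | 1.067 | 1.118 |
| 2 | 1.247 | 1.414 |

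A parent with no drift but event SD 1.3 scores 1.30, above the 1.118 of a parent who steps by a full SD. Matching 1.30 takes a step of 2√(1.69 − 1) = 1.66 SD.

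**Step 4: across a cohort.** The documents give no variance components, so these inputs are assumptions: 4,000 simulated parents, 4 waves, 32 events per wave, mean event SD 1, and between-parent CV of event SD 0.2. The SD of true wave shifts (τ) was varied.

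| τ | Drift share of pooled variance | Score vs wave-averaged consistency | Score vs true drift | SD of wave means vs true drift |
|---|---|---|---|---|
| 0.2 | 3% | 0.99 | 0.04 | 0.53 |
| 0.3 | 6% | 0.98 | 0.11 | 0.71 |
| 0.5 | 15% | 0.93 | 0.32 | 0.88 |
| 0.8 | 32% | 0.75 | 0.62 | 0.95 |

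Three waves give nearly the same. The CV matters. At τ = 0.8, CV 0.1 gives 0.50 with consistency and 0.80 with drift, while CV 0.3 gives 0.85 and 0.47.

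**Step 5: both scores in one model.** Variance inflation is 1/(1 − r²). Against period-specific consistency at CV 0.2 and τ of 0.23–0.5, r is 0.82–0.87 and inflation is about 3.1–4.2. It falls to 2.2–2.6 if event SD also varies between waves (CV 0.15), and to 1.9–2.7 with 16 events per wave. At other CVs with 32 events it is 1.4–2.0 (CV 0.1) and up to 7.5 (CV 0.3).

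**The case against.** The strongest reply has four parts.

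- **The score is not pure noise.** Because b_i is held constant over waves, wave shifts stay in the residuals, so the score does carry drift. If drift is large and parents differ little in event SD, it follows drift better than consistency. This stands. A reader might infer that the score measures meal-to-meal noise instead of maintenance; the model as written does not support that, and dominance by noise depends on variance components that the documents do not give.
- **Collinearity is easily overstated.** Wave-averaged consistency at r of 0.93–0.99 implies 7- to 50-fold inflation (1/(1 − 0.93²) ≈ 7; 1/(1 − 0.99²) ≈ 50). The plan defines consistency by period and does not say that it will be averaged over waves. Period-specific scores are the natural reading, and they give the smaller figures in step 5. This also stands.
- **The construction is only an example, in a condensed article.** This does not rescue it. The sentence before the example already commits to the same z score approach, no other definition is given, and the stated meaning conflicts with the stated formula. That is a conflict in the text, not a detail left to a fuller document.
- **Reach is limited.** There is no formal primary end point, and the primary HEI models use cluster indicators. It would be too strong to infer that those models are invalid: endurance reaches them only as one k-means input. It does enter the longitudinal HEI models directly.

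**Conclusion.** The point holds in a limited form. As defined, the endurance score mixes within-wave fluctuation with between-wave change and is blind to direction. Both facts follow from the model as written and need no variance assumption, nor does the possibility of misranking. They are enough to conflict with the score's stated meaning and with the contrast with short-lived use in hypothesis 4.

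How far the score duplicates consistency is conditional. Under the assumed values at CV 0.2 it largely does so while drift is up to about 15% of pooled variance, and much less at about 32%. Variance inflation against period-specific consistency is then about 2- to 4-fold, which is material but short of near-collinearity.

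**What to change.** Keep residual spread (SD, IQR, entropy) for consistency only. Fit the multi-wave model with person-by-wave effects and define endurance by two quantities:

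1. the between-wave variation of each parent's wave means net of event noise, shrunken because there are at most four waves;
2. the parent's signed slope over 0, 6, 12 and 24 months, so that loss and gain of a practice are told apart.

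Use these in place of the pooled residual spread in the longitudinal HEI models and as the k-means input.

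The change needs only analysis-plan wording and code; no new data are required, and collection is expected to run through November 2026. The downside is precision. A complete day requires only two event responses, so a wave may hold as few as 2 × 8 = 16 events. With 16 events the raw SD of wave means correlates only about 0.4–0.8 with true drift under the assumed values (CV 0.2, τ 0.23–0.5). Person-level endurance should therefore be reported with its uncertainty.

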#### Power Analysis

Given that the goal of this study is to describe patterns and associations and not evaluate a particular intervention, there is no formally defined primary end point. Hence, our power analysis focuses on describing the effect sizes that can plausibly be detected with the given analytic sample size of 200 families (accounting for approximately 20% attrition from our baseline sample).

Key outcomes are the mean levels of the 4 food parenting practice domains. With our sample size, 95% CIs for these means based on the total sample will have a margin of error of +0.17 or –0.17 SDs, corresponding to a small effect size per usual guidance [62]. For the clustering analyses, most participants will have at least 32 longitudinal observations spanning 8 days of data collection. Hence, we anticipate having an adequate sample size to accurately calculate individual summaries of the mean use, consistency, and endurance of food parenting practices, which will be used in the k-means clustering algorithm. To ensure that we can adequately characterize clusters based on demographic characteristics, we plan to restrict our clustering approaches so that they identify no more than 5 clusters, yielding an average cluster size of at least 30 participants; we will also restrict the minimum cluster size to 15 participants.

We calculate the detectable effect size of an analysis comparing mean child HEI between 2 groups of size n=100, for example, comparing families above and below the median of food parenting consistency or endurance. We have 80% power to detect a difference of 0.4 SDs, corresponding to the difference of approximately 4.7 units in total HEI given an HEI SD of 11.6 units in children aged 2 to 4 years enrolled in the NET-Works study [63]. For comparing 2 groups of size n=50 (eg, quartiles), we will have 80% power to detect a difference of 0.57 SD, or 6.7 HEI units. Power for associations between continuous summary measures of food parenting practices and total HEI will be higher.

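### The clustering plan returns three to five food parenting patterns even if parents form one homogeneous group, so the predicted distinct patterns cannot fail to appear

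*Protocol article*

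**What the plan says.** The second hypothesis (Results, Hypotheses) reads: "Distinct patterns in food parenting approaches will emerge; distinct pattern features will include mean levels of engagement in specific food parenting practices". It then adds consistency and endurance as further features of a pattern.

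The Overview of the Statistical Analysis Plan takes the same features (domain scores, consistency metrics and endurance metrics), which "will be used as inputs to a k-means algorithm". The range is stated as "We will apply the k-means algorithm with a modest number of clusters (3-5"), and the reason given is "to ensure that the resulting groups are of sufficient size to accurately characterize them". On choosing within the range: "Cluster stability metrics and qualitative assessment of the scientific meaningfulness of the clusters will be used to choose a final number of clusters". The clusters are then summarised and compared descriptively on food parenting practices and on demographic and family characteristics.

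The Power Analysis section caps the solution so that "they identify no more than 5 clusters, yielding an average cluster size of at least 30 participants", and sets a minimum cluster size of 15.

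The clusters are carried forward to the Healthy Eating Index (HEI) analyses: "Our primary models will include the subgroup indicators classifying parents according to food parenting practice patterns". The same paragraph also puts continuous consistency z scores into the period-specific models and endurance z scores into the longitudinal models. It lists average domain scores as a further option.

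**The concern.** A prediction that groups exist is informative only if the analysis could have shown none. Here one cluster is not a candidate, and neither are two. No stability level is named below which clustering would be abandoned, and no comparison with a population without groups is planned. If parents differ only by degree, the plan still divides them into three to five pieces, describes those pieces as patterns and enters them in the primary diet models. Readers could then take a division imposed by the method for types of parent found in the data. The article intends its findings to inform feeding guidance and later trials, so that misreading would matter.

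**Working it through.** **1. The plan's own figure.** With 200 families and at most 5 clusters, the average size is 200/5 = 40, which satisfies the stated bound of at least 30 (150/5 = 30 would be the limit). The figure is consistent.

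**2. Does group size justify the range?** Size supports an upper cap. It cannot support the lower limit: one cluster has 200 families and two average 200/2 = 100, both larger than 40.

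**3. Can a result without groups occur?** K-means partitions the data into exactly k sets. With k limited to 3, 4 or 5, the answer is 3, 4 or 5. This needs no simulation and no assumption.

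**4. Would the other criteria expose the absence of groups?** Data were simulated from one multivariate normal population. The document gives n = 200, k = 3–5 and the minimum size of 15. The number of inputs (4 or 12) and their equal correlation (0 or 0.5) are assumptions, because the document gives neither. There were 40 data sets per setting, with bootstrap Jaccard stability computed on 12 of them.

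| Inputs, correlation | k | Minimum size 15 met | Inputs differing at p<0.05 | Mean Jaccard |
|---|---|---|---|---|
| 4, 0 | 3 / 4 / 5 | 100 / 100 / 100% | 95 / 99 / 100% | 0.57 / 0.57 / 0.55 |
| 4, 0.5 | 3 / 4 / 5 | 100 / 100 / 95% | 100 / 100 / 100% | 0.84 / 0.68 / 0.59 |
| 12, 0 | 3 / 4 / 5 | 100 / 100 / 100% | 85 / 90 / 96% | 0.44 / 0.39 / 0.36 |
| 12, 0.5 | 3 / 4 / 5 | 100 / 95 / 78% | 100 / 100 / 100% | 0.85 / 0.73 / 0.62 |

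All k clusters were returned in 100% of runs. Every run had at least one input with p below 1e-10. The p-values only gauge how different the clusters would look, since the plan compares them descriptively. A separate simulation with 12 inputs at correlation 0.4 and k = 3 gave a mean Jaccard of 0.83.

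The minimum size seldom blocks a solution. Stability is low when inputs are uncorrelated but high at k = 3 when they are correlated, with no groups present in either case.

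**5. Does a one-group reference work?**
- *False claims.* The within-cluster sum of squares was compared with single-Gaussian data of the same covariance (4 inputs, k = 2–5, 39 reference sets, p ≤ 0.05). Structure was declared in 0 of 101 group-free data sets at correlation 0 and 0 of 106 at 0.5, so 0 of 207. In another run, a gap statistic that includes k = 1 chose one group in 14 of 15 group-free data sets at each of correlations 0.2 and 0.4.
- *Clear groups.* With three groups 3 or 4 SD apart and 4 inputs, the reference test declared structure in 116 of 116 and 109 of 109, so 225 of 225.
- *Moderate groups.* With 12 inputs, k = 3 and N = 200, the sum-of-squares rule declared structure in 0 of 30 data sets at 1.5 SD, 0 of 30 at 2 SD, 7 of 30 at 2.5 SD and 28 of 30 at 3 SD.

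**The case against.** The article does not say that the existence of clusters tests the second hypothesis. The Power Analysis section describes the aim as descriptive, with no formal primary end point, and k-means is offered as a way that might separate subsets of parents. Stability and meaningfulness are named, and a condensed article may leave their detailed use to a fuller plan. This much stands: the plan should not be read as containing a formal confirmatory test. It does not remove the problem. K-means is the only method given for forming parent patterns, its inputs match the features in the hypothesis, and the text fixes both the range and the purpose of the stability metrics.

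Two stronger readings are tempting, and the documents support neither.

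- *Continuous scores appear only in secondary models.* A reader might infer this from the description of the primary models. The same paragraph names individual-level summary measures as the main predictors and places consistency and endurance z scores beside the cluster indicators.
- *Clustering loses power for the HEI.* This depends on the comparator. With HEI correlated 0.2 with the mean of 12 inputs, a test of that exact mean had 79–83% power. An analyst would not know that composite, and the plan contains no such score. Entering the 12 scores jointly gave 35–41%, against 49–67% for the clusters. A general power loss is not shown.

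It is also fair that stability would sometimes warn the analyst (0.36–0.57 with uncorrelated inputs). The plan attaches no consequence to that warning.

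**Conclusion.** The point holds in a limited form. Under the stated range, three to five patterns are reported with certainty, whatever the data, and their differences on the input scores are largely built in. That follows from the method and needs no assumption. How reassuring the stability metrics would look depends on the assumed number and correlation of inputs: at k = 3, mean Jaccard in group-free data ran from 0.44 to 0.85. The finding concerns what may be claimed from the clusters. It does not show that the clusters are useless as a descriptive summary or that the HEI models are invalid.

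A reader might also infer that failing a one-group check would establish a continuum. It would not, because the check detected few or no groups at about 2 SD separation or less in the 12-input simulations.

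**What to change.** In the clustering paragraph of the Statistical Analysis Plan:

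- Let k run from 1 to 5.
- State that distinct patterns will be claimed only if the chosen solution beats a one-group reference. Name one in advance: a gap statistic that includes k = 1, or the sum of squares compared with single-Gaussian data of the same covariance.
- If it does not, report that distinct groups were not demonstrated and describe the clusters as a descriptive partition of possibly continuous scores. Report the continuous-score HEI models already planned alongside the cluster models with equal prominence.
- State that failing the check does not show that practices vary continuously, and do not let it switch the primary predictor automatically.

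The cost is a few lines of code and a paragraph of text, with no new data. Data collection is expected to run through November 2026, so the rule can be set before the full follow-up is analysed. There are two downsides: the second hypothesis may be reported as not supported, and moderately separated real groups may go undemonstrated at this sample size.

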 could reflect the average level of stress reported from signal surveys responded to in the 3 hours preceding the given event survey. We will fit separate models for each domain score during each data collection period; to increase power, we will also fit combined models that incorporate responses across multiple data collection periods. Single-predictor models (involving 1 type of momentary predictor, eg, stress) as well as multipredictor models will be considered. Time windows will be adjusted based on the observed response patterns of data, and if the momentary predictor data are overly sparse, multiple imputation will be used to fill in missing *W*values. In exploratory analyses, we will investigate whether momentary predictors interact with each other or with fixed and summarized individual characteristics (ie, consistency and endurance *z* scores) to impact food parenting practices. This will allow us to explore whether the strength of associations between momentary predictors and food parenting practices varies based on individuals’ levels of volatility in these practices.

Some participants may respond sporadically to event prompts, resulting in gaps between event prompt responses, which make it difficult to assess longitudinal patterns. We will begin by characterizing missing data patterns by participant and temporal factors, including the end-of-day prompts asking participants to indicate why they did not respond to prompts on a given day. Then, we will define and analyze a subset of “regularly responding” individuals for which there is sufficient data to characterize between-day fluctuations in food parenting practices, for example, a subset of individuals who have at most 2 days of event prompt nonresponse during their data collection period. To explore overall patterns and associations with non-EMA outcomes, we will augment this regularly responding set with data from individuals with more sporadic response patterns but who, based on their responses to end-of-day prompts, more plausibly have responses missing at random (eg, reported “forgot” rather than “too stressed”).

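### Model M2 gives each momentary predictor one coefficient, which blends between-parent with within-parent association, while hypothesis 5 is about shifts within a parent and within the day

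*Protocol article*

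**What the plan says.** The model is in the Protocol article, Statistical Analysis Plan, Overview: "The main statistical approach will be to fit longitudinal linear mixed models of the form: (M2", printed as D_ij = β0 + β1·W_ij + β2·X_i + b_i + ε_ij.

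- **W_ij** is a vector of momentary predictors, "which will be derived by summarizing signal surveys within fixed time windows before the event". In the worked example the variable "could reflect the average level of stress reported from signal surveys responded to in the 3 hours preceding the given event survey".
- **X_i** is defined at model M1, where it "is a set of baseline characteristics for person" i.
- **b_i**, also defined at M1, "is a person-specific random effect" and enters additively, so it is a random intercept.
- **Tests**: unless stated otherwise, "hypothesis tests will be conducted using a 2-sided α level of .05".

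The section mentions no parent-mean term, centring or random slope. Its exploratory analyses will "explore whether the strength of associations between momentary predictors and food parenting practices varies based on individuals" differ in volatility, using interactions with the consistency and endurance scores.

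Hypothesis 5, in the Results section, reads: "Parents will shift within the day from supportive feeding practices toward unsupportive feeding practices in response to momentary predictors".

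**The concern.** Two different facts can make β1 non-zero. A parent may feed differently at moments when they are more stressed than is usual for them. Or parents who are generally more stressed may feed differently from parents who are generally calm. Hypothesis 5 is about the first, and M2 has a single coefficient for both. The two slopes need not be equal, and the article does not argue that they are.

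The Power Analysis section separates covariates that vary only between individuals from momentary predictors, but M2 does not make that separation inside W.

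The Discussion says the findings will inform interventions that respond to momentary factors. A stable difference between parents, read as a momentary shift, would be a poor basis for such an intervention. Slopes of opposite sign could equally hide a real momentary effect.

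**Working it through.** **1. Inputs from the article.** There are 200 families with at least 32 observations each, and 200 × 32 = 6400, which matches the stated total. The 32 counts event or signal responses, four a day for 8 days. A complete day needs only 2 event prompts (Ecological Momentary Assessment section), so the minimum number of domain-score records is 2 × 8 = 16 per parent. Detectable differences at 80% power are 0.55 items for a between-person covariate and 0.14 items for a momentary predictor.

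**2. Variance components.** The 0.14 comes from a simulation whose parameters are not printed, so it cannot be reproduced directly. Components consistent with both figures can be back-solved, assuming a covariate prevalence of 0.5, a momentary covariate that varies only within parents, and 1.96 + 0.84 = 2.80:

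- σ² = (0.14/2.80)² × 6400 × 0.25 = 4.00
- τ² = (0.55/2.80)² × 200 × 0.25 − 4.00/32 = 1.80
- ICC of D = 1.80/5.80 = 0.31 (0.31 to 0.42 for prevalences of 0.2 to 0.5)

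**3. Weight of the between-parent association.** In a random-intercept model β1 = (1 − w)·within + w·between, with

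w/(1 − w) = (SSB/SSW) / (1 + n·τ²/σ²).

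Per parent, with ρ the ICC of W, SSB = nρ + (1 − ρ) and SSW = (n − 1)(1 − ρ). For n = 32 and ρ = 0.4, SSB = 13.4, SSW = 18.6 and the denominator is 1 + 32 × 0.31/0.69 = 15.4. The ratio is 0.047, so w = 4.5%. The article does not give ρ; 0.2 to 0.6 is assumed.

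| Records per parent | ρ = 0.2 | ρ = 0.4 | ρ = 0.6 |
|---|---|---|---|
| 32 | 1.9% | 4.5% | 9.3% |
| 16 | 3.9% | 8.7% | 16.9% |

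The weight is sensitive to the outcome ICC. At an ICC of D of 0.1 and ρ = 0.6 it is 26% (32 records) or 38% (16).

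**4. Effect on the test.** Simulation of 200 parents, 1000 runs, σ² = 4, τ² = 1.8, total SD of W = 1, true within-parent effect zero, variance components estimated. The between-parent slope is in items per SD of W. Because the residual SD is 2 items, slopes of 0.5 and 1.0 are 0.25 and 0.5 residual SD.

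| Records | ρ | Between slope | Mean β1 | M2 rejects | Centred term rejects |
|---|---|---|---|---|---|
| 32 | 0.4 | 0 | 0.001 | 4% | 5% |
| 32 | 0.4 | 0.5 | 0.022 | 11% | 6% |
| 32 | 0.4 | 1.0 | 0.036 | 22% | 7% |
| 32 | 0.6 | 0.5 | 0.042 | 21% | 6% |
| 32 | 0.6 | 1.0 | 0.070 | 46% | 5% |
| 16 | 0.4 | 0.5 | 0.039 | 14% | 4% |
| 16 | 0.4 | 1.0 | 0.067 | 33% | 4% |
| 16 | 0.6 | 1.0 | 0.137 | 74% | 4% |

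For slopes of 0.3 to 0.5 residual SD and ρ of 0.4 to 0.6, the range is roughly 12–44% at 32 records and 17–75% at 16. A repeat with 2000 runs gave 12–49% and 17–70%, so the upper ends are approximate.

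**5. Opposite signs.** With a within-parent slope of +0.1, a between-parent slope of −0.5, 32 records and ρ = 0.4, mean β1 falls to 0.078. Power falls from 89% (centred) to 66%.

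**6. Random structure.** If the within-parent slope varies between parents and no random slope is fitted, type I error for its mean at 16 records is about 7% for a slope SD of 0.1 and 16–25% for 0.3, depending on scaling. Omitting a day-within-parent intercept has no single direction. Type I error is 11–18% for a weekend indicator, 6–11% for a W clustered by day and 2–3% for a meal indicator.

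**The case against.** The case for leaving M2 alone has real content.

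- **Centring is not expressly ruled out.** The display that defines W_ij did not survive in the text at hand, and the stress example only says what the variable could be. The surrounding text describes time windows alone, however, and the printed equation has no parent-mean term. This lowers certainty without removing the point.
- **The blend is small on average.** At 32 records the spurious mean β1 is 0.022 to 0.070, against a stated detectable difference of 0.14 items (a binary-covariate figure, so only a rough comparison). Pooling periods should lower the between-parent weight further. This stands for the estimate, but less so for tests at the 5% level.
- **X_i absorbs part of it.** The survey measures income, socioeconomic status and parent mental health. A reader might infer that M2 would report any income or chronic-stress difference as a momentary effect. That goes too far: only the between-parent association left after X_i contributes, and the slopes in the simulation must be read that way.
- **The study is descriptive**, with no formal primary end point. This limits the severity, but hypothesis 5 is still a directional claim that the plan will test.

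Three other stronger readings are not supported. The plan does not state that the effect varies across parents; it will explore whether it does. A missing day intercept does not always make standard errors too small. Scenarios with 8 events per parent have no basis in the stated schedule.

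**Conclusion.** The point holds as a mismatch between the printed model and hypothesis 5. M2's coefficient equals the within-parent effect only if the within- and between-parent slopes are equal. The contamination of the estimate is modest at the planned record counts, but the contamination of the test can be material when a strong between-parent association remains after adjustment.

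The sizes rest on an assumed ICC of W, assumed between-parent slopes, a within-parent effect of exactly zero and an outcome ICC back-solved from the Power Analysis. The article gives none of these directly. The direction of the problem does not depend on them.

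Separating parents' averages from their deviations is also not enough for the hypothesis as worded. A deviation from the parent's period mean still mixes bad days against good days with shifts inside a day. Severity: should-fix.

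**What to change.** - **Split each momentary predictor into three terms**: the parent-by-period mean, the parent-day mean's deviation from it, and the event's deviation from the parent-day mean. Base the within-day claim of hypothesis 5 on the last term.
- **Where signals per day are too few for a day mean**, use the deviation from the parent-by-period mean and describe the result as within-parent, not within-day.
- **Allow for differing slopes** with a random slope for the deviation term, or use cluster-robust standard errors by parent.
- **Add a day-within-parent intercept** where the covariate is constant or clustered within day, such as day of week in M1.

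The cost is a few lines of text and code. Data collection is unaffected and still under way, so the change can precede analysis.

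There is a small loss of sensitivity. If 0.14 items assumed purely within-parent variation, the detectable within-parent difference becomes 0.14/√((1 − ρ) × 31/32), which is about 0.16, 0.18 or 0.22 items for ρ = 0.2, 0.4 or 0.6.
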